### 5.3 Definition of Adverse Event

An adverse event (AE) is defined as any unanticipated problem involving risks to study participants or others. An adverse event, therefore, can be any unfavorable or unintended sign, symptom, disease, syndrome, abnormal laboratory finding, or concurrent illness that

emerges or worsens relative to the infant's pretreatment baseline, whether or not it is considered to be related to the medicinal product.

All conditions that exist prior to administration of the study vaccine (pre-existing conditions) will be recorded in the infant's medical history to establish baseline. Day-to-day fluctuations in pre-existing conditions that do not represent a clinically significant change in the infant's status will not necessarily be reported as adverse events.

Any adverse change from the infant's baseline condition (determined from screening evaluations conducted to confirm study eligibility) that occurs following the administration of the study vaccine will be considered an adverse event. This includes the occurrence of a new adverse event or the worsening of a baseline condition, whether or not considered related to the study vaccine. Intermittent conditions such as headaches may be present on Study Day 0 but may represent an adverse event if the intensity or duration of the event is worse than usual following receipt of study vaccine. Adverse events include but are not limited to: adverse changes from baseline that represent increases in toxicity grade according to the Toxicity Table (see protocol appendices), adverse changes in the general condition of the infant, signs and symptoms noted by the infant's caregiver, concomitant disease with onset or increased severity after study vaccine administration, and changes in laboratory safety parameters occurring after study vaccine administration.

**The reporting period for all adverse events is specified in Section 3.** Adverse events will be reported on the Adverse Event Case Report Form (CRF) using a recognized medical term or diagnosis that accurately reflects the event. Adverse event evaluations will be reviewed by the principal investigator or by a designated medically qualified practitioner. Adverse event CRF pages are to be completed by members of the study team designated in writing by the principal investigator. The onset and resolution dates of the event and action taken in response to the event will be documented. All adverse events must be followed until resolution is demonstrated or until the end of the appropriate AE reporting period. The resolution date will be recorded on the CRF as the last date on which the infant experienced the adverse event or, if unresolved by the last day of the appropriate reporting period, the resolution date will be recorded on the CRF as "ongoing." Information recorded on the CRF must be substantiated in the source documents. If an adverse event evolves into a condition that becomes "serious," it will be designated as serious on the Adverse Event CRF and a SAE Report (SAER) form will be completed.

#### 5.4 Assessing Severity

The safety concepts of "severity" and "seriousness" are distinct concepts (see Section 5.8). Severity refers to a degree of clinical manifestation. "Seriousness" refers to defined outcomes from an adverse event. A severe adverse event is not always serious and a serious adverse event is not always severe.

For all adverse events, the investigator (or designee, who is a healthcare professional; is someone the investigator deems qualified to review adverse event information, to provide a medical evaluation of the event, and to classify the event based upon medical judgment and

the severity categories described below) is responsible for assessing the severity of the event and the causal relationship of the event to the study vaccine.

The **severity** of all adverse events, including clinical findings and abnormal laboratory values, will be classified as one of the following grades:

1. **Mild**
2. **Moderate**
3. **Severe**

A Toxicity Table is provided in the protocol appendices for the assessment of severity of specified adverse events. The Toxicity Table Adverse Event Grades do not correlate directly with the classical severity grades of mild, moderate and severe. FOR THE PURPOSES OF RECORDING EVENTS ON THE CRF, Toxicity Table Grade 1 events will be considered mild in severity, Toxicity Table Grade 2 events will be considered moderate in severity, and both Toxicity Table Grade 3 and 4 events will be considered as severe. In the Toxicity Table certain local reactions such as erythema (redness) and swelling are graded according to size. Laboratory values are graded according to level of deviation from the normal range.

For adverse events not listed in the Toxicity Table determination of severity requires some level of interpretation as outlined below. The degree of incapacity caused by the adverse event and the level of medical intervention required for treatment may be helpful in assessing the overall severity of the adverse event.

For example:

- “Mild” events are generally regarded as noticeable but have no impact on normal activities; they may or may not require over-the-counter treatment managed by the infant.
- “Moderate” events generally have some impact on an individual’s normal activities and may require general symptomatic medical intervention by a healthcare professional or by the infant.
- “Severe” adverse events may be incapacitating, leading to suspension of normal daily activities, and would generally require more immediate medical evaluation and intervention by a healthcare professional.

A change in severity of an adverse event will not be recorded as a new adverse event. Only the highest severity level that occurs during the entire period of the adverse event will be recorded on the CRF with the onset and resolution dates encompassing the entire duration of the event.

## 5.5 Assessing Causal Relationship (Relatedness)

For all adverse events, the investigator and the sponsor (the local medical monitor) will determine a **causal relationship**, to the study vaccine without knowledge, for blinded studies, of whether MVA85A/AERAS-485, placebo, or active control was administered. A number of factors will be considered in making this assessment, including: 1) the temporal relationship of the event to the administration of the study vaccine 2) whether an alternative etiology has been identified and 3) biological plausibility. The investigator will use the following guidelines to assess the causal relationship of an adverse event to study vaccine:

- **Not Related** to study vaccine (i.e., there is no evidence of a causal relationship; another etiology is known to have caused the adverse event. The alternative etiology should be documented in the infant's study record).
- **Unlikely Related** to study vaccine (i.e. there is less than a reasonable possibility that the adverse event was caused by study vaccine).
- **Possible** relationship to study vaccine (i.e., there is a reasonable possibility that the adverse event was caused by study vaccine. There must be a plausible mechanism for the event to be related to study vaccine. The evidence is inadequate to accept or reject, or favors rejection of, a causal relationship; an association exists between the event and the study vaccine but there may also be an alternative etiology, such as characteristics of the infant's clinical status or underlying condition).
- **Probable** relationship to study vaccine (i.e., it is likely that the adverse event was caused by administration of the study vaccine. The evidence favors acceptance of a causal relationship; an association exists between the event and receipt of the study vaccine and there is a plausible mechanism for the event to be related to the study vaccine, and an alternative etiology is not apparent).
- **Definite** relationship to study vaccine (i.e., the study vaccine is known to be the cause of the adverse event. The evidence establishes a causal relationship; an association exists between the event and receipt of the study vaccine and there is a plausible mechanism for the event to be related to the study vaccine, and causes other than the study vaccine have been ruled out).

The principal investigator and the local medical monitor both determine causality. It is expected that communication and consultation may occur in the assessment of the causality of adverse events. The greatest degree of causal relationship (definite > probable > possible > unlikely related > not related) determined by either the investigator or local medical monitor after their discussions will determine the ultimate classification of the adverse event. Definite, probable and possible are considered to be related. Not related and unlikely related are considered to be unrelated.

Every effort should be made by the investigator to determine the existence of any pre-existing conditions (e.g., mild nausea or headache on Study Day 0 with onset prior to study vaccination) that must be taken into consideration when assessing causal relationship of an adverse event. Pre-existing conditions should be recorded in the CRF as baseline history and substantiated by appropriate source documentation. Intermittent conditions such as headaches or menstrual pain may not be present on Study Day 0 but may represent an adverse event if the intensity or duration of the event is worse than usual following study vaccine.

## 5.6 Definition of Adverse Reaction

An adverse reaction is an adverse event judged to be related to study vaccine (see Section 5.3 for adverse event definition).

**Related adverse events (adverse reactions) are defined as those judged by the investigator or local medical monitor to be possibly, probably, or definitely related to study vaccine.**

**The reporting period for all adverse events and adverse reactions is the 28-day post-vaccination follow-up period.** Adverse events and adverse reactions will be reported on an Adverse Event CRF using a recognized medical term or diagnosis that accurately reflects the event.

### **5.7 Solicited Adverse Events and Injection Site Reactions**

Solicited adverse events are events that a subject (or a subject's parents/guardians) is specifically asked about. These adverse events are commonly observed soon after receipt of vaccines. For this study, solicited adverse events include site of injection reactions, diarrhea, vomiting and others. Solicited adverse events of local injection site reactions will be considered causally related to study vaccine (adverse reaction).

**The reporting period during which *solicited* adverse events will be obtained is the immediate 7 day period following each vaccination.** The solicited adverse event reporting period begins with the day of vaccination. All infant's parents/guardians will be provided a diary card to record information regarding occurrences of these specific events. Solicited adverse events and temperature will be recorded by the infant's parents/guardians in a diary beginning on the day of vaccination through the specified time period. The diary card, when completed, will serve as source documentation for reporting on the Adverse Event CRF. Solicited adverse events will be entered on the Adverse Event Case Report Form.

Adverse events and solicited adverse events including assessment of local injection site reactions will be assessed by the investigator for severity, causal relationship to the study vaccine, possible etiologies, and whether the event meets criteria as a serious adverse event (and therefore requires immediate notification to the medical monitor).

Presence of ulceration and/or scarring at the site of injection and lymphadenopathy of the injection arm are considered to be adverse events that are causally related to the study vaccine and are of special interest. Site of injection ulceration (including presence of drainage) and axillary lymphadenopathy will be actively evaluated during each visit through the end of the study. These events will be recorded on the Adverse Event Case Report Form.

In the event that the clinical presentation meets the definition of a serious adverse event, in addition to the Adverse Event Case Report Form, a SAE Report must be completed and the event reported per protocol instructions.

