## EVALUATIONS AND FOLLOW-UP

Infants who are randomized at Study Day 0 will be followed up on a regular schedule at Study Day 7 ( $\pm 2$  days), Study Day 28 ( $\pm 5$  days), Study Day 84 ( $\pm 5$  days) and every 84 days ( $\pm 7$  days) thereafter until the end of the study. Specific evaluations at each follow-up will be determined by the study group to which an infant is enrolled. All infants will be followed for adverse events for 28 days after vaccination and for serious adverse events and the development of tuberculosis until the end of the study.

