**Table 1 Infant Schedule of Evaluations and Treatments Study Day -84 to Study Day 84 for the Safety Cohort**

| Study Day                     | -84 a | -35 a | -14 a | 0   | 7   | 28   | 84  |
|-------------------------------|------------------|------------------|------------------|-----|-----|------|-----|
| Minimum Age (Days)            | 42               | 91               | 112              | 126 | 133 | 154  | 210 |
| Written Informed Consent      | X                |                  |                  |     |     |      |     |
| Verify Eligibility Criteria   |                  |                  |                  | X   |     |      |     |
| Medical History               |                  | X                |                  |     |     |      |     |
| Physical Examination          |                  | X                |                  |     |     |      |     |
| HIV-1                         |                  |                  | 3                |     |     |      |     |
| Vital Signs                   |                  |                  |                  | X   | X   | X    | X   |
| Weight                        |                  | X                |                  | X   | X   | X    | X   |
| Injection Site Photograph     |                  |                  |                  | X   |     |      |     |
| Study Vaccine Administration  |                  |                  |                  | X   |     |      |     |
| Serum Chemistry b  |                  |                  | 1.0              |     | 1.0 | 1.0  |     |
| CBC, Differential, Platelets  |                  |                  | 1.0              |     | 1.0 | 1.0  |     |
| QuantiFERON (Gold in tube)    |                  |                  | 3                |     |     |      |     |
| Immunology Samples            |                  |                  |                  |     |     | 8    |     |
| Solicited Adverse events      |                  |                  |                  | X   | X   |      |     |
| Assess Adverse Events         |                  |                  |                  | X   | X   | X    |     |
| Serious Adverse Event Reports |                  |                  |                  | X   | X   | X    | X   |
| Site of Injection Examination |                  |                  |                  | X   | X   | X    |     |

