| Blood volume (mL) per visit   |                  | 6                | 8               |     |     | 8   |     |

a Written informed consent must be obtained prior to initiation of study screening activities and may be obtained prior to Day -84. Medical history/physical exams and blood collection for HIV-1 and QuantiFERON testing must be completed within 35 days prior to Study Day 0; blood collections for baseline immunology must be completed within 7 days prior to randomization.

After study day 84 study enrollees will be visited by a study member at least every 84 days until the end of the study. At these visits, infants will be weighed, assessed for the occurrence of a new SAE, and assessed for admission to a case verification ward for suspected tuberculosis. Any infant with a cohabiting household member in which the diagnosis of tuberculosis has been made or any infant that has 1) weight loss in last two months, 2) cough for more than two weeks without improvement, 3) failure-to-thrive, or 4) conversion to a positive QuantiFERON test or positive Mantoux test will be admitted to the case verification ward for diagnosis of tuberculosis.

A QuantiFERON test will be drawn on Study Day 336 for all subjects followed to Study Day 336 and on the last clinic visit in all infants without the clinical diagnosis of tuberculosis. Follow up of all infants will be terminated at the next scheduled study visit after the last enrollee completes 15 months of follow-up (Study Day 420).

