#### **3.5.2 Clinical Assessments and Laboratory Tests**

An examination of the injection site and draining lymph nodes of injection arm will be performed 60 minutes after study vaccine/control administration and at Study Days 7 and 28. Infants will have vital signs recorded at Study Days 7, 28, and 84. Infants will also have their weight recorded prior to vaccination on Study Day 0 and then again on Study Day 7, 28, 84 and every 84 days thereafter.

Laboratory evaluations are planned for only the infants enrolled in the Safety Cohort (Study Group 1). The Safety Monitoring Committee may determine that additional infants need to enroll in this cohort after a review of the safety data from these infants. Blood for hematology and serum chemistry will be collected at screening and on Study Days 7 and 28. All laboratory samples will be processed according to SOPs provided by the local clinical laboratory.

Prior to any blood draw, all infants will be evaluated for clinical signs of anemia (e.g., palmar pallor). If the evaluation suggests anemia in an infant, the infant will have hemoglobin evaluated by fingerprick. If the hemoglobin obtained by fingerprick is  $< 9\text{g/dL}$ , then blood will not be drawn from that infant at that visit.

All infants randomized to the study will have blood for QFT-G collected during screening, again on Study Day 336, during evaluations for TB in the CV ward, and on the last scheduled visit for each infant.

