### 3.5.4 Safety Evaluations

Through the 28-day period following vaccination, all **adverse events** observed by the investigator (or designee) or reported by the infant's parents/guardians spontaneously in response to a direct question or recorded on the diary card, will be medically evaluated and documented in terms of a medical diagnosis on the Adverse Event CRF.

Through the entire study period, all **serious adverse events** observed by the investigator or reported by the infant's parents/guardians spontaneously or in response to a question will be medically evaluated and documented on the appropriate adverse event CRF.

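### Section 5.7 requires ulceration and axillary nodes to be evaluated at every visit to end of study, but the schedule places the examination only at Days 0, 7 and 28 and the 28-day adverse-event window makes no exception for them

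*Protocol*

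**What the plan says.** Section 5.7 names ulceration or scarring at the injection site and lymphadenopathy of the injection arm as related events of special interest. For ulceration and axillary nodes it adds an active duty: "Site of injection ulceration (including presence of drainage) and axillary lymphadenopathy will be actively evaluated during each visit through the end of the study". It also requires the findings to go on the Adverse Event CRF.

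The text that sites work from day to day is narrower:

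- **Section 3.5.2:** a single inspection covers both site and nodes, and its timing is fixed in these words: "draining lymph nodes of injection arm will be performed 60 minutes after study vaccine/control administration and at Study Days 7 and 28".
- **Tables 1-5 (Section 3.1):** the row "Site of Injection Examination" is marked at Days 0, 7 and 28 and blank at Day 84.
- **Section 3.1, visits after Day 84:** "At these visits, infants will be weighed, assessed for the occurrence of a new SAE, and assessed for admission to a case verification ward".
- **Abstract, Evaluations and Follow-up:** "All infants will be followed for adverse events for 28 days after vaccination and for serious adverse events", the latter continuing to the end of the study.
- **Section 3.5.4:** the collection rule opens "Through the 28-day period following vaccination, all" adverse events. Section 5.2 repeats it.
- **Section 5.6:** "The reporting period for all adverse events and adverse reactions is the 28-day post-vaccination follow-up period".
- **Section 5.3:** "The reporting period for all adverse events is specified in Section 3".

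**The concern.** Safety is the primary objective, and these are the local events that the protocol itself singles out for active search. Section 3.5 tells sites to follow infants on the visit schedule of their study group. A site that does so would stop examining the injection site and nodes after Day 28. It would also find no instruction in Section 3 to report a new non-serious event after that day.

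What is at stake is detection. A late case that reaches the CRF falls within the primary safety variable of Section 7.5.1, which covers events recorded after vaccination. A case that nobody looked for does not, and no analysis plan can recover an examination that was not done. Both planned safety reviews by the Safety Monitoring Committee (Sections 5.1.5 and 7.8) are triggered by completion of Day 84, the visit where the conflict is direct.

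**Working it through.** The protocol gives no figure to reproduce. The check sets the texts side by side and counts visits.

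**Step 1: visit calendar.** Sections 3.1 and 3.5.2 give Days 0, 7, 28 and 84, then every 84 days. Section 3.1 ends follow-up no earlier than Study Day 420, which it equates with 15 months. An infant followed to Day 420 has visits at Days 0, 7, 28, 84, 168, 252, 336 and 420, which is 8.

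**Step 2: compare the two rules at each visit.**

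| Visit | Section 5.7 | Section 3.5.2 and Tables 1-5 | Section 3.1, later visits | Result |
|---|---|---|---|---|
| Days 0, 7, 28 | evaluate | examination scheduled | not applicable | agree (3) |
| Day 84 | evaluate | not listed in 3.5.2; cell blank in all five tables | not applicable | direct conflict (1) |
| Days 168, 252, 336, 420 | evaluate | not listed in 3.5.2; outside the tables | not listed | conflict by omission (4) |

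8 − 3 = 5 visits without the scheduled examination, and 5 = 1 + 4.

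**Step 3: longest follow-up.** The protocol allows up to 39 months. If a month is 28 days, as in 15 months = Day 420, this is 39 × 28 = Day 1092, with 1092 / 84 = 13 visits from Day 84 on. The total is 3 + 13 = 16 visits, 13 of them without the examination. With calendar months (about Day 1187) the count is 17 visits, 14 without. The month length is an assumption. On either reading only Day 84 is a direct conflict.

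**Step 4: is stopping at Day 28 just shorthand?** The same paragraph of Section 3.5.2 carries vital signs to Day 84 and weight to every 84-day visit after that. The tables leave the Assess Adverse Events row blank at Day 84 too, but mark serious adverse events there. Assessments are extended where extension was meant, so the stop at Day 28 reads as deliberate.

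**Step 5: does the reporting window allow for these events?** Section 5.3 sends staff to Section 3. Section 3.5.4 gives 28 days for adverse events and the whole study for serious ones only. Section 5.6 includes adverse reactions in the 28 days, and Section 5.7 classes these events as related. Neither section refers to the other.

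**Step 6: what would still be captured after Day 28?**

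- Serious events, to end of study.
- Events already open at Day 28, under Section 5.13. Section 5.3, however, lets an event be closed as ongoing at the end of its reporting period.
- Events that parents report under the untimed opening instruction of Section 3.5.7, although its reminder list goes back to 28 days.
- Findings at the physical examination of infants admitted for case verification (Section 3.5.6).

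None of these is the active evaluation at each visit that Section 5.7 orders. What remains exposed is the new, non-serious late event.

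**The case against.** The strongest reply is that the protocol does order the evaluation. Section 5.7 is current and explicit, and it can be read as the specific rule that prevails over a general schedule. Much of this stands. A reader might infer that the late examination is missing from the plan altogether. It is not, and the risk is uneven conduct by sites that work from the schedule.

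Second, four of the five visits are silence. Section 3.1 is headed as a summary, its list for later visits does not say only, and other duties sit outside it, such as the anaemia check before blood draws in Section 3.5.2. This also stands, which is why only Day 84 is called a direct conflict.

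Third, the word all in Section 5.6 cannot be literal, because serious events run to end of study, and Section 5.7 sets its own periods by event class. This shows that exceptions exist. But the exception for serious events is written out in the abstract and in Sections 3.5.4 and 5.2, and none is written there for ulceration or nodes.

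Fourth, the consequence is not shown. Section 1.4 reports that most earlier local reactions resolved within 1 week. It would be tempting to express the gap as a share of calendar days or as the number of infants enrolled. Neither measures loss: most days have no visit, and the document gives no rate of late-onset events. Nor does the text support an inference of bias between groups, since both blinded groups follow the same schedule, and no efficacy result is touched.

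**Conclusion.** The inconsistency is real and should be fixed. To Day 420, 5 of 8 visits lack an examination that Section 5.7 requires: 1 (Day 84) by direct conflict with Section 3.5.2 and Tables 1-5, and 4 by omission in Section 3.1. The 28-day window in the abstract and in Sections 3.5.4, 5.2 and 5.6 has no exception for these events. New, non-serious ulceration or axillary nodes arising after Day 28 may therefore not be looked for systematically.

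The count rests on the protocol's visit calendar and on the minimum follow-up to Day 420. The consequence rests on sites following their schedule where it differs from Section 5.7. The number of events missed cannot be estimated and may be low. The documents do not support saying that late events would go wholly unrecorded or that the safety comparison would be distorted.

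**What to change.** Add the injection-site and axillary-node examination at Day 84 and at each later 84-day visit in Section 3.1, Section 3.5.2 and Tables 1-5. State in the abstract, Sections 3.5.4, 5.2 and 5.6, and the reminder list of Section 3.5.7 that these events are reported to end of study. Put the same statement in a footnote to the Assess Adverse Events row of each table. Section 5.3 can stay, since it points to Section 3, and Section 7.5.1 needs no change.

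The cost is protocol wording and a brief inspection at visits that already take place, with no added visits or blood. There is one downside. Section 5.7 counts lymphadenopathy of the injection arm as related, so late nodes from other causes would be counted as related in both blinded groups.

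Cutting Section 5.7 back to Day 28 would also remove the contradiction, but it would gain no safety information on events that the protocol marks as being of special interest.
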